#### Randomisation/blinding

The process of randomisation is performed centrally by the Institute for Biometry. A randomisation list is created and assigns the patients to either the control group or the study group. When the surgical procedure arrives at the point at which EVICEL™ treatment has to be performed in the active group (after conventional haemostasis), the investigator then initiates the randomisation and queries the patient’s assignment at the Institute for Biometry by phone. This procedure allows the statement to be made that the operation prior to the application of EVICEL™ is concealed and performed without any bias.

In this RCT, the patients will be blinded but owing to the nature of the intervention the surgeons clearly cannot be blinded.

The treating surgeons will conduct the therapy in a way that complies with the single-blinded design of the study. In the rare case of a spinal anaesthesia, it will be ensured that patients will have no opportunity to realise whether they receive the medicinal product under investigation (IMP) or not. The medical team involved in the operation and patient’s care is responsible for keeping the treatment blinded. The nurses, physiotherapists and physicians collecting data after surgery will also be blinded to the treatment allocation.

### Subject withdrawal

As the application of EVICEL™ is conducted only at a single time point in a three-step procedure, subjects cannot be withdrawn from the IMP treatment. The only exceptions are complications occurring during the operation, leading to an immediate cessation of EVICEL™ use.

Patients undergoing a thromboembolic or any other event demanding anticoagulation that exceeds the standard prophylaxis measures during the first 7 days after surgery will be recorded as having the smallest Hb value before anticoagulation. Patients receiving anticoagulation during the operation will be recorded as having the largest Hb difference of the control group. The same procedure applies to patients receiving any kind of blood product during or after the operation. Because in nearly all cases there will be a blood sample collection prior to a transfusion or to a change in anticoagulation medication, these patients are expected to account for <1 % of all patients and will be recorded separately.

The following procedure applies to patients receiving any kind of blood product or an extended anticoagulation medication during or after the operation. Patients receiving blood transfusions during the operation but before randomisation will not be randomised. Patients receiving blood transfusions during the operation and after randomisation will be recorded as having the largest Hb difference of the control group. Patients receiving a blood transfusion after the operation would require measurement of Hb level before transfusion. Patients deteriorating despite transfusion will be recorded as having the smallest observed Hb level. For each transfusion, the Hb value at the time of transfusion, the reason for the transfusion (with specification of the symptoms) and the time of transfusion will be documented precisely.

Patients with an intraoperative deviation from the agreed haemostatic procedure (use of EVICEL™, electrocoagulation, or of the tourniquet deviating from the agreement, e.g. in the case of surgery lasting >2 h) will not be enrolled. In most cases, it is foreseeable before randomisation that the operation will probably take longer than 2 h; therefore, those patients will not be randomised, and the percentage of subjects not included because of the duration of surgery is expected to be <1 %.

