### Primary and secondary study endpoints

The primary endpoint of this study is postoperative blood loss after TKR, measured by the difference in Hb levels at baseline (recorded in the 3 days prior to randomisation) with respect to the detected minimum in the first 7 days postoperatively and compared between the study group and the control group. During this period, blood samples will be taken regularly according to the in-house protocol, and results will be compared with control values derived from patients treated under the same conditions but without the use of EVICEL™. During the operation, all factors that affect the postoperative level of Hb will be documented.

Secondary endpoints are the need for at least one allogeneic blood transfusion or one autologous transfusion, the ROM of the operated joint, the postoperative use of analgesics, time until wound healing, clinical outcome scores, length of hospital stay, and the overall cost of the treatment.

A follow-up measurement of ROM will be conducted 3, 6 and 12 months after surgery. The ROM of the operated joint in the study and the control group will be measured using the angle of maximum flexion. Factors that might influence the ROM (for example, the use of a peripheral nerve block) will be documented and might lead to exclusion from the secondary endpoint calculation (for example, preoperative maximal flexion <90°). The need for at least one blood transfusion will be compared between the study and the control group to demonstrate whether or not EVICEL™ reduces the need for transfusions. Furthermore, it should be shown that the use of analgesics (according to the WHO pain ladder [4]) can be reduced by treatment with EVICEL™ and that the time until the wound is completely dry is shorter. In addition, it should be shown that the clinical outcome in the EVICEL™ group is better than that in the control group. Clinical outcome is assessed by two different clinical outcome scores, the clinician-completed Knee Society Score (KSS) and the patient-completed Knee Injury and Osteoarthritis Outcome Score (KOOS) [5, 6].

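### The primary-endpoint score of a patient transfused after surgery is not uniquely fixed, and no reading measures that patient's own blood loss once bleeding continues

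*Protocol article*

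**What the plan says.** Primary and secondary study endpoints defines the outcome as blood loss, "measured by the difference in Hb levels at baseline (recorded in the 3 days prior to randomisation) with respect to the detected minimum" over the first 7 postoperative days. Statistical methods analyses that difference by ANCOVA with baseline Hb as covariate. Neither section mentions transfused haemoglobin.

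Subject withdrawal holds the scoring rules for special cases, in two consecutive paragraphs.

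- The first paragraph scores patients who need extended anticoagulation in the first 7 days on their smallest Hb before it. It then says "Patients receiving anticoagulation during the operation will be recorded as having the largest Hb difference of the control group", followed directly by "The same procedure applies to patients receiving any kind of blood product during or after the operation". It closes by noting that a sample will nearly always precede a transfusion or a change of anticoagulation, so that "these patients are expected to account for <1 % of all patients and will be recorded separately".
- The second paragraph treats intraoperative and postoperative transfusion separately. For the former: "Patients receiving blood transfusions during the operation and after randomisation will be recorded as having the largest Hb difference of the control group". For the latter: "Patients receiving a blood transfusion after the operation would require measurement of Hb level before transfusion", and then "Patients deteriorating despite transfusion will be recorded as having the smallest observed Hb level".

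Postoperative procedure already has the case report form capture the units transfused, the date, the Hb before transfusion and the reason.

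**The concern.** Two things are wrong with the text as it stands.

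First, the paragraphs do not agree. The nearest antecedent of the sentence on any blood product is the worst-case value, and that sentence expressly includes the period after the operation. The following paragraph keeps the worst-case value for intraoperative transfusion and points to observed Hb values for postoperative transfusion. A third reading is also possible: the antecedent could be the earlier rule, the smallest value before anticoagulation.

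Second, under either rule that uses observed Hb, a value taken after transfusion contains donor haemoglobin and is not corrected for it. Blood lost after the transfusion is partly or wholly hidden.

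These patients tend to be the heavier bleeders, and the protocol expects fewer of them in the EVICEL arm. The choice of reading can therefore move the primary contrast, in opposite directions, and it would be made after the data exist unless the text is settled first.

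**Working it through.** **Step 1: the plan's own figure.** From Sample size calculation: means 25 and 37 g/l (difference 12), SD 15, two-sided 0.05, power 90 %. Normal approximation: n = 2 × (1.960 + 1.282)² × 15² / 12² = 32.8, so 33 per group. With the noncentral t distribution, power is 0.893 at 33 and 0.902 at 34. The stated 34 per group reproduces.

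**Step 2: one patient under each reading.** Illustrative values: baseline 135 g/l, Hb before transfusion 78, two units at an assumed 10 g/l each.

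| Later lowest Hb | Fall in own blood | Smallest observed Hb | Smallest Hb before transfusion |
|---|---|---|---|
| 75 (deteriorates) | 135 − (75 − 20) = 80 | 135 − 75 = 60 | 135 − 78 = 57 |
| 80 (keeps bleeding) | 135 − (80 − 20) = 75 | 135 − 78 = 57 | 57 |
| 98 (bleeding stops) | 135 − 78 = 57 | 57 | 57 |

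Under the worst-case reading the score is the largest control difference in every row, whatever this patient lost. The observed-minimum rule is right when bleeding stops. It is short by 18 to 20 g/l in the first two rows.

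**Step 3: effect on the contrast, analytically.** If a g/l is masked per affected patient, and shares qC and qE of the control and EVICEL arms are affected, the contrast falls by a × (qC − qE).

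- 10 × (0.05 − 0.01) = 0.4 g/l, power 0.88
- 20 × (0.10 − 0.02) = 1.6 g/l, power 0.80
- 20 × (0.20 − 0.05) = 3.0 g/l, power 0.68
- equal shares: no loss

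The shares are assumed and these powers hold SD at 15. Masking also trims the upper tail of the falls, so they overstate the damage (step 4).

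**Step 4: observed-minimum reading, simulated.** Postoperative procedure gives the site's criterion as Hb below 6 g/dl, or 6 to 8 g/dl with more than mild symptoms.

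*Simulation A* (assumed baseline 137, SD 12, floor 110; about 65 % of the fall by the first of four draws; two units at 10 g/l each; 400,000 patients per arm):

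| Transfused below | Contrast, observed minimum | Contrast, own blood | Loss |
|---|---|---|---|
| 80 g/l, 50 % of such patients | 37.19 − 25.86 = 11.33 | 37.59 − 25.95 = 11.64 | 0.31 |
| 80 g/l, all | 36.86 − 25.73 = 11.13 | 37.61 − 25.91 = 11.70 | 0.57 |
| 90 g/l, 70 % | 36.05 − 25.45 = 10.60 | 37.51 − 25.92 = 11.59 | 0.99 |

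A rebuild of these scenarios, with later draws assumed at 85, 95 and 100 % of the fall, gives power at 34 per group with and without correction of 0.902 and 0.901, 0.905 and 0.902, and 0.902 and 0.890.

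*Simulation B* (assumed baseline mean 130 or 140, SD 12, floor 110; SD of the fall 15; rise from transfusion 10 or 20 g/l; everyone transfused on crossing the trigger):

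- Trigger 60 g/l: contrast 11.9 to 12.0, power unchanged.
- Trigger 80 g/l: contrast 10.5 to 11.5. The SD falls from 15.0 to between 13.5 and 14.4, so power drops by at most about 1.6 points (0.902 to 0.886).
- Trigger 100 g/l: contrast 7.7 to 10.1, power 0.80 to 0.88. This is an extreme, since the protocol calls transfusion at 8 to 10 g/dl unlikely.

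The first two triggers bracket the site's criterion: a loss of 0 to 1.5 g/l.

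**Step 5: worst-case reading, simulated.** With 34 per arm, trigger 80 g/l and every transfused patient given the largest control difference, the mean contrast is 14.2 g/l (baseline 130; about 25 % of controls and 9 % of EVICEL patients transfused) or 12.9 g/l (baseline 140; about 12 % and 3 %). It widens from 12.

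**The case against.** The best defence has five parts.

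- **The rule is narrower than it looks.** The smallest-observed-Hb sentence covers only patients who deteriorate despite transfusion. For the others, the required sample captures the fall up to the transfusion. This stands, as the last row of the table in step 2 shows; only later bleeding is lost.
- **The worst-case value was probably meant for the few without a prior sample.** The under-1 % remark supports that intention. The sentence does not state the limit, however, and it names the postoperative period. Nor can the under-1 % figure be read as a transfusion rate, because its justification is that a prior sample usually exists.
- **The endpoint is by definition the detected minimum, with transfusion a separate secondary endpoint.** This is fair, and it is a reason to report a corrected analysis beside the planned one rather than in its place.
- **The masking is conservative and small.** If more controls are transfused, it pulls toward no difference, and power hardly moves under the stated criterion. Both stand, on that condition.
- **The planned 12 g/l may already contain masking.** If the published decreases used for the sample size were observed values, subtracting masking from them counts it twice. The source is not available, so this stays open.

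**Conclusion.** The point holds in a limited form. Subject withdrawal does not fix one score for a patient transfused after surgery, and none of its readings measures that patient's own loss when bleeding continues. On the worst-case reading the contrast widens to about 12.9-14.2 g/l. On the observed-minimum reading it shrinks by about 0.3-0.6 g/l (simulation A) or 0-1.5 g/l (simulation B) under the site's criterion, with at most about 1.6 points of power lost. Both shifts require more transfusions among controls than among EVICEL patients. Baseline Hb, transfusion rates and rise per unit are not in the documents.

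A reader might infer more: that the plan understates loss in every patient transfused after surgery and so dilutes the treatment effect, by as much as 1.0 g/l or 8 % of 12. The documents do not support that. The direction depends on which sentence governs and on the transfusion rates by arm. The 8 % figure comes from transfusing 70 % of patients below 90 g/l, in a range where the protocol calls transfusion unlikely. Nor do they support calling the trial underpowered on this ground.

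**What to change.** In Subject withdrawal, state one scoring rule for transfusion after the operation. Delete the sentence extending the same procedure to any blood product, or limit it so that the worst-case value does not apply to a patient who has an Hb measured before transfusion.

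Add one pre-specified analysis of the primary endpoint. Each Hb taken after a transfusion is reduced by a fixed expected rise per red-cell unit already given, for example 10 g/l with a range of 7 to 12 g/l. The fall is baseline minus the lowest corrected value over the 7 days. Report it beside the observed-minimum result.

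The cost is a few sentences. Units, date and pre-transfusion Hb are already on the case report form, Subject withdrawal also asks for the time, and Trial status says recruitment has not begun. The downside is small: the per-unit rise is assumed, and it covers red-cell units only, not other blood products.

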### Insurance

Mandatory patient insurance for this trial according to AMG § 40 (3) has been obtained. Because of this, any damage to patient health during the conduct of the study will be insured, with a maximum amount of coverage of €500,000 per patient. This covers all damage that may occur to the patient either indirectly or directly as a result of the study medication or interventions in connection with the RCT.

### Overview of the medical product under investigation

EVICEL™ is a fibrin sealant kit consisting of two human plasma-derived components, human clottable protein containing mainly fibrinogen and fibronectin (component 1), and human thrombin (component 2), both produced by Omrix Biopharmaceuticals S.A. [8].

EVICEL™ is a further development of QUIXIL, which has been approved for marketing in 14 EU countries since 2003, first in the UK in 1999. One difference between EVICEL™ and QUIXIL is the final composition of the fibrinogen component, but the thrombin component remains the same. The fibrinogen component of QUIXIL contains the synthetic antifibrinolytic agent tranexamic acid (TA), which inhibits the degradation of fibrinogen. However, because TA is potentially neurotoxic QUIXIL is contraindicated for use in neurosurgery and all procedures where contact with the cerebral spinal fluid (CSF) and dura mater might occur. By specifically removing plasminogen the need for stabilisation with TA is avoided, and EVICEL’s fibrinogen is formulated without TA. Its protein concentration is 30 to 50 % higher, requiring the submission of a new application for marketing authorisation.

EVICEL is indicated as an adjunct to haemostasis for use in patients undergoing surgery, when control of bleeding by standard surgical techniques (such as sutures, ligatures or cautery) is ineffective or impractical. EVICEL™ is intended for epilesional use only, and the dosage should always be oriented towards the underlying clinical needs of the patient. The manufacturer recommends a dosage of 5 ml for TKR.

### Risks

The following potential risks may occur when administering fibrin sealants:Immunogenicity, hypersensitivity, allergic reaction and anaphylaxis, and the possible development of antibodies against components of fibrin sealants. The risk is markedly increased when fibrin sealants are used repeatedly or in patients with a known hypersensitivity to the active substances or to any of the excipients.Thromboembolic events due to accidental intravascular administration.Transmission of infections. Standard measures to prevent infections resulting from the use of medicinal products prepared from human blood or plasma include the selection of donors, screening of individual donations and plasma pools for specific markers of infection, and the inclusion of effective manufacturing steps for the inactivation/removal of viruses. The measures taken are considered effective for enveloped viruses such as HIV, hepatitis C virus and hepatitis B virus, and for the non-enveloped hepatitis A virus. The measures taken may be of limited value against non-enveloped viruses such as parvovirus B19.Complications related to infections or thromboembolism, postoperative wound complications.Tissue adhesion at undesired sites owing to incorrect product application.

## Discussion

The clinical significance of and rationale for the conception of this study was the fact that after TKR only the ‘visible’ blood loss is usually known, whereas ‘hidden’ blood loss often is underestimated. In a study involving 101 patients undergoing TKR, the hidden blood loss contributed 49 % to the ‘true’ total blood loss from bleeding into the tissues or into the joint [1].

A decrease in postoperative Hb levels may be caused by either intraoperative or postoperative blood loss. EVICEL™ is used at the end of the surgery, so that postoperative blood loss is the only fraction that might be affected by its use. Therefore, the study was designed to keep intraoperative blood loss as low as possible in order to provide better conditions for the effect of the fibrin sealant and to achieve meaningful results. For this reason, all operations were planned to be conducted in a bloodless field.

Several clinical studies have shown that the preceding fibrin sealant, QUIXIL, significantly reduces blood loss in patients undergoing total hip or total knee replacement [7, 9–11]. In contrast, another study evaluating blood loss and number of blood transfusions in patients undergoing TKR could not prove any benefit from the use of QUIXIL [12]. In a study with 165 patients undergoing TKR, the authors concluded that the use of platelet gel and fibrin sealant improves ROM, reduces hospital stay and may reduce the incidence of arthrofibrosis [2]. However, during the planning phase of the study protocol presented here, there were no data concerning the newer fibrin sealant EVICEL.

Owing to delays in obtaining approval for the study from the competent national authority associated with product changes, by the time the study was finally ready for submission there were several published studies in the literature evaluating the effects of EVICEL in TKR. Randelli *et al*. [13] reported in their RCT that the application of EVICEL reduces neither perioperative blood loss nor the need for allogeneic blood transfusion. Skovgaard *et al*. [14] found that the drain output in knees treated with fibrin sealant and those treated with placebo was similar, and that no statistically significant differences could be seen regarding either swelling, pain, strength of knee extension or ROM.

In another study [15], however, the results suggested that transfusion rates in anaemic patients undergoing TKR were significantly lower than in a control group, and that the use of EVICEL resulted in a significant reduction of blood loss. In their meta-analysis, Liu *et al*. [16] reported that the use of fibrin sealants in TKR significantly reduced total blood loss, drainage blood loss and haemoglobin loss as well as transfusion rates.

In conclusion, a literature search delivers inconsistent and ambivalent results indicating that, despite the presence of comparable studies, there is still a need for high-evidence studies clarifying the role of fibrin sealants in TKR, as proposed in the study protocol presented here.

## Trial status

This RCT was designed as an investigator-initiated study for which Hannover Medical School was assumed to be acting as sponsor. The study was funded by Ethicon Inc., the parent company of Omrix Biopharmaceuticals, which produces the IMP. A contract was signed and initial financial support was provided according to the contract terms, which included approval by the Independent Ethics Committee. Approval by the national competent authority was not obtained following feedback from the European Medicines Agency. When the issues were resolved, the study was prepared for resubmission to the national competent authority. However, in the meantime, ETHICON changed their business strategy and further funding was withdrawn. Therefore, the study has not yet started patient recruitment.

## Abbreviations

AE: adverse event
AMG: Arzneimittelgesetz (German Drug Law)
ANCOVA: analysis of covariance
BMI: body mass index
CBC: complete blood count
CRF: case report form
CRP: C-reactive protein (blood marker of infection)
CSF: cerebral spinal fluid
DIC: disseminated intravascular coagulation
DRKS: Deutsches Register Klinischer Studien (German Registry of Clinical Trials)
Hb: haemoglobin
HIV: human immunodeficiency virus
ID: identification
IMP: investigational medicinal product
INR: International Normalised Ratio
ITT: intention to treat
KSS: Knee Society Score
KOOS: Knee Injury and Osteoarthritis Outcome Score
LOCF: last observation carried forward
OR: odds ratio
PP: per protocol
PTT: partial thromboplastin time
RCT: randomised controlled trial
ROM: range of motion
SAE: serious adverse event
TKR: total knee replacement
TA: tranexamic acid
